### ****4.3.9 Summary of objectives and methodologies for sub study two****

| **Objectives** | **Methods** | **Indicator/data to be collected** | **Target population** | **Sample size** |
| --- | --- | --- | --- | --- |
| 1. Determine the common pre-and neo-natal homecare practices and their determinants among lactating women in Masindi and Kiryandongo districts | **Key Informant Interviews** | **Common homecare practices** | **TBAs, Elderly caregivers** | **6 TBAs and 6 Elderly caregivers-3 each from Masindi & Kiryandongo** |
|  | **Structured Interviews** | **Different homecare practices received by lactating mothers during the pre-intra-and neonatal period** | **Lactating women** | **823 lactating mothers** |
| 1. Explore the rationale for homecare practices offered to pregnant women and newborn babies during the pre-,intra- and immediate post-natal period in the districts of Masindi and Kiryandongo | **Key Informant Interviews** | **Rationale/explanations for the common homecare practices offered to pregnant women and their newborn babies** | **TBAs. Elderly care givers** | **6 TBAs and 6 Elderly caregivers-3 each from Masindi & Kiryandongo** |
| 1. Document detailed experiences of care received by lactating women during the pre-and neo-natal period | **In-Depth Interviews** | **Detailed experiences of different age groups of lactating mothers regarding care offered to them during pre-intra-and immediate postnatal period** | **Sub groups of lactating women (adolescents 10-19 years and adults-20 and above)** | **Total: 30 lactating women-20 adolescents and 10 adult lactating women** |

# 4.4 Sub study three-the intervention

**Engaging Community Health Workers to provide a combined package of prenatal education interventions at primary care facilities with the use of mobile phone reminders from health workers and measure its effects on timely return visits, completion of four ANC visits, institutional deliveries and newborn care practices-a community intervention trial**

## 4.4.1 Introduction

The ultimate intervention will be based on data obtained from the two formative surveys and; based on our own knowledge about the context of Masindi and Kiryandongo and the subject of maternal and newborn care. The first study with health workers will inform the design of re-orienting health services at the antenatal clinic, while the community survey will form a basis for the appropriate educational messages to be delivered at the ANC clinics.

Primary outcomes of interest in this study are timely return ANC visits, completed four ANC visits, institutional delivery, and neonatal homecare practices. Secondary outcomes are post intervention community and health workers perceptions about the educational intervention offered by CHWs at the primary care facility.

The educational intervention will consist of **i)** a promotional team of community health workers supervised by a health assistant providing educational interventions at the primary care facility and; **ii)** the promotional team at the health centre using mobile phone reminders through Community Health Workers to pregnant women at the households.

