### 4.4.7 Study variables

## Independent/factor:

(i) Routine ANC care available in the health facilities (standard care);

(ii) *Promotional team* giving additional education care to pregnant women with periodic mobile phone reminders.

*Dependent/outcome variables*

1. Timely return ANC visits (return within seven days of the scheduled appointment date)
2. Completion of the four recommended ANC visits
3. Institutional deliveries
4. Newborn care practices:
5. Provision of warmth to the newborn
6. Initiation of breastfeeding within one hour of birth
7. Care for the cord
8. Immunization for the newborn-Polio 0 & 1; BCG within the neonatal period

We will, at the end of the study, assess perceptions of individual women who have participated in this intervention towards the integrated package by administering the tool described by Howie and others ([Howie J, Heaney D et al. 1998](#_ENREF_42)) elaborated in annex 15 (the Patient-Enablement Initiative (PEI).

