### 4.4.8 Sample size

Using the formula for cluster randomised trials suggested by Hayes and Bennett ([Hayes and Bennett 1999](#_ENREF_36)),

**n = D(Z_α/2_ + Z_β_)^2^[π_0_(1- π_0_) + π_1_(1- π_1_)]/ (π_0 +_  π_1_)^2^** where

- **n** = number of participants in each arm,
- **D** = the design effect of 2.5,
- **Z_α/2_** = 1.96,
- **Z_β_ = 0.84,**
- **π_0_ =** current rate of institutional deliveries, 23.5%
- **π_1_** = estimated rate of institutional deliveries after the intervention, 33.5%

Substituting in the formula, we obtain a sample size of 788; allowing for a 10% loss-to-follow up we estimate a total population of 868 participants per arm. Further substituting in the formula for required number of cluster, C

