**C=1+(Z_α/2_ + Z_β_)^2^[π_0_(1- π_0_)/n + π_1_(1- π_1_)/n + k^2^(π_0_^2^ _+_ π_1_^2^)]/ (π_0 +_ π_1_)^2^**

Substituting for n=868, we arrive at a cluster number of 8 per arm; two arms will therefore require 1,736 participants distributed between 16 health centres; implying an average of 108 pregnant women enrolled per health centre for the entire four months. This will necessitate recruiting an average of 27 pregnant women per health centre per month.

This sample is based on the following assumptions:

- A degree of error, 0.05
- (95% confidence interval, **Z_a_** =1.96),
- the power to detect a significant difference between two comparison groups of 80% (**Z_a/2_** =0.84) to detect a 10% difference;
- **π_0_**, the current prevalence of institutional deliveries 23.5% ([DHO 2010](#_ENREF_28));
- **π_1_**, expected prevalence of institutional deliveries after the intervention 33.5% and
- A design effect **D,** 2.5 and
- Coefficient of variation between clusters of the same group **k_m_,** 0.25

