**4.4.10 Data management and analysis**

At the end of each trail day, data will be collected, sorted and checked for consistency and for completeness. Open-ended questions will be categorized. All data collected will be entered in Epi-data soft ware package and exported to stata 8.2 soft ware package for more analysis. This analysis will be done in stages: univariate analysis ,where frequencies of variables will be generated and tabulated to establish the extent of use of these ANC services in the standard health centre setting compared to the second arm where extra education, and telephone remainders will be made. This level will also show the factors influencing timely return ANC visits, completion of the four recommended ANC visits, institutional deliveries and newborn care practices (Provision of warmth to the newborn, Initiation of breastfeeding within one hour of birth, Care for the cord and Immunization for the newborn-Polio 0 & 1; BCG within the neonatal period). At bi-variate level of analysis, cross tabulations will be run to establish associations between variables of interest. Chi-square tests will be used to establish significant associations. At multi variate analysis, all variables that will be found to be statistically significant at bi-variate ,will be subjected to the multivariate model (logistic) to control for confounding. The analysis will be run to get Odds Ratio values, 95%CI for the OR, and the respective p-values will be presented. Finally the primary outcomes of interest will be compared between the two arms i.e. a standard arm and the new trial arm upon which conclusions will be drawn.

*Quality Control*

To control quality of data to be collected,(completeness, correctness and consistency), the following measures will be undertaken:

Research assistants will be selected and trained by the principal investigator, questionnaires will be pre-tested for one day in a few selected health centres in Masindi and Kiryandongo. Completed questionnaires will be collected and checked by the principal investigator. Data collection will be carried out under strict supervision of the principal investigator. Data editing will be done and corrections will be made there at the selected health centres.

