**4 months**

Primary Outcomes

Outcome measures among study participants:

1. Timely ANC return visits
2. Completed 4 visits
3. Institutional deliveries
4. Homecare newborn care practices
5. Immunisation status of the newborn

868 Participants per arm Total = **1,736**

Follow-up

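### Sub study three has four unranked primary outcomes but is sized on institutional delivery alone, so the stated 5% error and 80% power do not describe the trial's overall conclusion

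*Protocol*

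**What the plan says.** **Number of primary outcomes.** Section 4.4.1 gives four, in no stated order: "Primary outcomes of interest in this study are timely return ANC visits, completed four ANC visits, institutional delivery, and neonatal homecare practices". Section 4.4.6 repeats the four. The study profile in 4.4.11 lists five under its primary outcomes heading, with "Immunisation status of the newborn" as a separate line. Annex 9 goes back to four and joins immunisation to newborn care.

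**Content of the newborn outcome.** Section 4.4.7 breaks newborn care into four parts. The first is "Provision of warmth to the newborn". The next two are breastfeeding within an hour of birth and cord care. The last is "Immunization for the newborn-Polio 0 & 1; BCG within the neonatal period". No score, composite or minimum number of practices is given. The intervention procedure in Annex 15 lists further items to assess, including cutting of the cord, pre-lacteal feeds and care-seeking for illness.

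**Sizing.** Section 4.4.8 uses one outcome, the "current rate of institutional deliveries, 23.5"%, with 33.5% expected after the intervention. Its assumptions include "A degree of error, 0.05", a "95% confidence interval" and 80% power. No other primary outcome has a target difference or a stated power.

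**Analysis.** Section 4.4.10 plans chi-square tests, then logistic models reporting odds ratios, 95% intervals and p-values. It ends: "Finally the primary outcomes of interest will be compared between the two arms", and says that conclusions rest on this comparison. It mentions neither an order of testing, nor an adjustment for the number of outcomes, nor how many outcomes must favour the intervention.

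**The concern.** Which outcomes are primary, and which of them sets the sample size, is protocol content. Here the count differs between sections, one of the four outcomes has no single definition, and only one is sized. A reader of the final report would take 5% and 80% as the operating characteristics of the trial, but they were derived for one of its four outcomes.

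Without a success rule, the effect depends on how the conclusion is reached. If one positive outcome of several suffices, false claims become more likely than 5%. If all must be positive, the trial is harder to win than 80% suggests. The protocol does not say which applies, so the choice could be made after the results are known.

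**Working it through.** **1. The plan's own sample size.** Inputs from 4.4.8: control rate 0.235, intervention rate 0.335, z-values 1.96 and 0.84, design effect 2.5.

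- Variance sum: 0.235 × 0.765 + 0.335 × 0.665 = 0.17978 + 0.22278 = 0.40255.
- n per arm = 2.5 × (1.96 + 0.84)² × 0.40255 / 0.10² = 789, against 788 stated.
- With 10% added: 789 × 1.1 = 868, as stated.

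This takes the squared difference in the denominator. The printed plus sign would give 24, so it was evidently not used. The 5% and 80% are thus reproduced for institutional delivery, on the plan's design effect.

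**2. If any one significant outcome is enough.** Assume each test is valid at two-sided 5% and the intervention affects none of the outcomes. For m independent tests the chance of at least one false positive is 1 − 0.95^m.

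| Outcomes tested | Independent | Correlation 0.3 | 0.5 | 0.7 |
|---|---|---|---|---|
| 4 (sections 4.4.1, 4.4.6, Annex 9) | 18.5% | 17% | 16% | 13% |
| 5 (study profile) | 22.6% | 21% | 18% | 15% |
| 7 (3 outcomes + 4 newborn components) | 30.2% | 27% | 23% | 18% |

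The correlated columns come from simulation with equally correlated normal test statistics. The correlations are assumed, because the protocol gives none. Only the row for four is firmly supported by the text.

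**3. If all four must be significant.** The chance of a false overall claim is then no more than 5%. Joint power cannot exceed that of the weakest outcome, so it is at most the 80% for institutional delivery. As an illustration only, four independent outcomes with 80% power each would give 0.8⁴ = 41%. The true figure cannot be computed, because the other three have no stated target difference.

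**4. What an equal split of alpha would cost.** For four outcomes the level is 0.05 / 4 = 0.0125 (z = 2.498). With 788 evaluable per arm and design effect 2.5, the effective size is 788 / 2.5 = 315.2 and the standard error is √(0.40255 / 315.2) = 0.0357.

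- Power at 0.05: Φ(0.10 / 0.0357 − 1.960) = about 80%.
- Power at 0.0125: Φ(0.10 / 0.0357 − 2.498) = about 62%.
- To restore 80%: 2.5 × (2.498 + 0.842)² × 0.40255 / 0.10² = about 1,122 evaluable per arm.

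**The case against.** **A separate analysis plan may settle this.** A multiplicity method or success rule is often left to that document, which is not shown, and its absence from the protocol is not the finding. What remains is what the protocol itself fixes: several unranked primary outcomes, counted differently in different sections, with one sized. An analysis plan would not remove that conflict.

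**The hypothesis is worded jointly.** The abstract links the four outcomes with a conjunction, which could mean that all are expected. On that reading type I error does not inflate. This stands, and it is why no single error rate can be attached to the trial. It moves the problem to joint power.

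**The outcomes are related.** The operational definitions treat consistent attendance as both timely and complete, and the introduction argues that consistent attendance leads to institutional delivery. Positive correlation is therefore likely, and 18.5% is an upper figure for four valid tests.

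**Sizing on one outcome is common.** This is fair. Taking the fourth-visit rate of 29.4% from section 4.1 and assuming a 10-point gain, the same calculation gives about 76% power, so a serious shortfall for that outcome is not shown.

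**Stronger readings.** A reader might infer a false-success rate of 19% to 30%, or 37% with the three vaccine doses tested separately (1 − 0.95⁹). The documents do not support these as the trial's error rate. No passage says that any one result suffices, and the 5% level per outcome is inferred from the sizing assumptions and the 95% intervals. The components are listed without being declared separate claims, and nothing says the vaccines are tested one by one. The fifth line in the profile may be no more than labelling, since the operational definitions and Annex 9 place immunisation with newborn care.

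**Conclusion.** The point holds in limited form. The protocol fixes four unranked primary outcomes, is inconsistent on whether immunisation is a fifth, leaves newborn care without a single definition, and sizes only institutional delivery.

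If any one result at 5% counts as success, the family-wise error for four outcomes is about 18.5% under independence and about 13% to 17% for assumed correlations of 0.7 to 0.3. It approaches 30% only if each newborn component is also claimed separately and the tests are independent. If all four must succeed, type I error is not inflated, and the consequence is a joint power that is unknown and no higher than 80%. These figures assume that each test is itself valid at 5%. Whether the chi-square tests are valid with clustered data is a separate matter and is not counted here.

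On either reading, the stated 5% and 80% belong to institutional delivery and not to the overall conclusion. This should be corrected, and it does not require a larger trial.

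**What to change.** Name institutional delivery as the single primary outcome. The trial is already sized on it, so 788 evaluable and 868 recruited per arm stay as they are and its test keeps the full 5%.

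Make timely return, four completed visits and one defined newborn-care outcome key secondary outcomes. State how the newborn components, including immunisation, combine into that one outcome. Either test the three with Holm (smallest p-value against 0.05 / 3 = 0.0167), after a significant primary result if error control across both tiers is wanted, or report them as estimates with confidence intervals and no success claim. Use the same list in 4.4.1, 4.4.6, 4.4.7, the study profile and Annex 9.

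The cost is that three outcomes lose primary status, and the hypothesis in the abstract and the objectives in 3.7 and 4.4.3 need matching wording. No women or data are added. If the investigators prefer to keep all four as primary, they should state whether all or any must succeed and give the resulting power. An equal split would need about 1,122 evaluable women per arm to keep 80% for institutional delivery.

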## 4.4.2 General objective

Based on the findings from our initial studies regarding maternal and newborn health, we aim to: measure the effect of a combined package of CHWs offering educational interventions with use of mobile cell phone reminders on selected maternal and newborn indices.

**4.4.3 Specific**

1. Determine the effect of CHWs offering a combined package of prenatal education and using mobile phone reminders on timely return visits, completed four ANC visits, institutional deliveries and newborn care practices in Masindi and Kiryandongo districts
2. Explore post-intervention perception of lactating women towards the application of the combined package of prenatal educational intervention and mobile phone reminders

# 4.4.4 Methodology

### 4.4.5 Study design

We will conduct a community trial involving two arms: a community intervention trial.

1. One arm receives the routine ANC care available in the health facilities (standard care); this normally involves the provision of technical ANC services (history taking, palpation, PMTCT), group health education sometimes, and appointment for the next visit; rarely providing targeted or individualised health education
2. A second arm will receive in addition a *promotional team* comprising of a staff with a promotional profile (in this case health assistant) and three other CHWs providing educational interventions to augment the technical ANC intervention provided by qualified staffs. Health workers and CHWs will have in their possession mobile cell-phones. The mobile phones will be used by health workers to call CHWs to make reminders about return ANC visits for prenatal women, due dates for institutional deliveries, as well as providing additional educational information to pregnant women through the CHWs and any other consultations the CHW may want to make with health workers.

*Study population:*

The population to be studied will be pregnant women in Masindi and Kiryandongo districts who enrol for antenatal care in the 16 selected health centres for the two trial arms, with each trial arm utilising 8 health centres

### 4.4.6 Inclusion and exclusion criteria:

*Inclusion:*

All pregnant women found to be up to 28 weeks of pregnancy in Masindi and Kiryandongo districts registered for ANC in the 16 selected health centres will be eligible participants. Gestational age will be estimated using the Last Normal Menstrual Period (LNMP) as volunteered by the pregnant woman and verified by palpation of height of fundus.

Pregnant women sampled for inclusion in to the study will be followed until one month after the termination of pregnancy and they will be assessed for the primary outcomes of interest: **i)**  *timely return ANC visits* **ii)** *completed four ANC visits*, **ii)** *institutional deliveries* and **iii)** *homecare practices for newborns*. The end point for the follow-up of study participants will be up to four weeks after termination of pregnancy (the neonatal period).

Although early initiation of ANC in the first trimester is known to allow sufficient time for delivering repeated educational messages, the gestation age of 28 weeks has been purposely chosen because a significant proportion of women (about 45%) in this region of Masindi and Kiryandongo make their first ANC visit in the second trimester ([DHO 2010](#_ENREF_28)).

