## 1.4 Prenatal educational interventions

Underlying challenges with achieving prenatal educational interventions are numerous: inadequate counselling during antenatal, limited access to care even when danger signs are recognised early and conflicting traditional care practices ([MOH 2010a](#_ENREF_60)).

Even when up to 97% of women attend ANC visit at least once, only 17% make the first visit in the first trimester; 34% of them initiate it late in the third trimester while 47% attend all the four recommended visits ([UDHS 2006](#_ENREF_85)). Late initiation and incomplete attendance of ANC visits at the health facility significantly compromise efforts of health education and counselling for prenatal women.

The high drop-out rates in ANC can, in many ways, be compared to high drop-out rates seen in pre-ART clinics attributed to low counselling at the various clinics. One such study conducted in Uganda showed that educational interventions and counselling is generally lacking in many health facilities ([Lubega, Nsabagasani et al. 2009](#_ENREF_55)) leading to high drop-out rates during HIV/AIDS care. The same argument could be extended to maternal and newborn health (personal communication).

Similar findings were shown in Tanzania ([Magoma M, Requejo J et al. 2010](#_ENREF_56)) where lack of sufficient educational interventions during ANC was associated with low utilisation of skilled delivery at birth. Some of the reasons advanced for the low counselling in health facilities are explained by the primary focus of health workers being on disease and its management rather than on people and their wider environment.

Studies conducted in Asia ([Choudhury and Ahmed 2011](#_ENREF_19)) among the ultra-poor populations suggests that specific sub-class of people required a tailored educational intervention in order to attain a behaviour change in the uptake of pre-and post-natal services.

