## 2.3 Delivery of the comprehensive ANC care model

Improving maternal and newborn survival by the delivery of an integrated comprehensive healthcare package through a continuum of care has been widely endorsed and advocated for ([WHO 2010](#_ENREF_113)). In this model a primary healthcare worker provides a series of both clinical and promotional interventions to a pregnant mother during ANC, through the intra-partum at delivery to the postnatal period.

Unfortunately, most pregnant mothers for varied reasons ([Waiswa P, Kemigisa M et al. 2008](#_ENREF_97)), attend the first antenatal visit and never return for subsequent visits, rarely completing the predetermined four visits for the entire gestation period. Moreover, many of them make the first visit late in to the second or third trimester ([WHO 2008a](#_ENREF_110)). This late attendance coupled with high attrition rates in ANC present a ‘missed opportunity’ for care-seeking mothers to receive a comprehensive package of preventive and promotional services.

Skilled attendance at birth although widely advocated for, amidst several health system challenges, has equally not gained any significance in sub Saharan Africa ([Waiswa P, Peterson S et al. 2010](#_ENREF_98))

A skilled attendant as defined by WHO is an accredited health professional, such as a midwife, a doctor or nurse ([WHO 2004](#_ENREF_114)). Inherent in this definition is the central role of the skilled attendant in the health system ([WHO 2004](#_ENREF_114)) acting as a link between the community and the tertiary level of care. During labour, only about 46% of the expected mothers get in to some contact with the formal healthcare system ([WHO 2009](#_ENREF_112)), a contact time that is usually inadequate to deliver all the important promotional and preventive health messages.

On the other hand, pregnant women and their newborn babies who never make any formal contacts with the healthcare system during the time of labour are faced with challenges related to practices and beliefs ([Choudhury and Ahmed 2011](#_ENREF_19)) such as early bathing of the baby, late initiation of breastfeeding, unhygienic practices ([Waiswa P, Kemigisa M et al. 2008](#_ENREF_97)) that are likely to jeopardise the health of both mother and the newborn. Moreover these risky practices are not just limited to the lower socio-economic class but have been shown to apply across all social classes ([Waiswa P, Peterson S et al. 2010](#_ENREF_98)).

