# Annex 15: SOPs: Standard Operating Procedure and intervention packages

### i) Standard operating procedure and intervention package for educational intervention during ANC

**(**[**Bhutta Z, Sajid S et al. 2011**](#_ENREF_10)**)**

When the pregnant women enter the clinic room

1. Identify pregnant women with all of the following conditions:
2. First visit of the current pregnancy,
3. Not more than 28 weeks of gestation
4. Administer the consent form
5. If she consents then open a file for her
6. Request for her ANC card
7. Enter all personal details available on the ANC card in to the file
8. Record any telephone contacts that you can use to access her in future

name, age, ethnicity, parity, LNMP, EDD, gestation age of the first visit, history of previous pregnancy outcome of the previous pregnancy (baby – alive or dead, mode of delivery), distance from the health facility, marital status, history of previous ANC attendance-Number of attendance, delivery (home, health facility, TBA etc).

Note the date for the next appointment, (all this information will be used to tailor the discussions)

-if she consistently attended all the expected milestones-then you find out what her motivation was to do so, and whether she plans to do the same for the current pregnancy;

- If not consistent-discuss the reasons for inconsistencies and help her to find a solution,

- diet during pregnancy-find out what foods are readily consumed and what she can easily afford, what foods could be prohibited during pregnancy (caution about antagonising cultures-you can find another acceptable alternative source of the food value) and discuss the importance for balances in diet, fruits, green vegetables, proteins and carbohydrates,

- Discuss work related activities-how much she does and who helps her with the routine household and garden chores.

- Discuss importance of ANC even when she has been attending consistently, the advantages of delivering in the health facility even when she has been delivering at the health facility,

- Birth preparation-clean clothes for the newborn (emphasis that clean does not mean new!-even old rages can be patched together washed clean, clean environment for the newborn,

- caring for the cord, dangers of applying substances to the cord,

- Pre-lacteal feeds-and its disadvantages-explain how breast milk eventually comes and the usefulness of colostrum.

- Discuss bathing of the new baby how soon and how to delay (delay up to 24 hours),

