- Immunisation of the child, polio 0, BCG etc.

- Recognition of a sick child-hot to touch, refusing to feed, crying unusually,

All these information should be derived from discussions with the pregnant woman-not as a set of instructions to be strictly followed-compromises should be made at every stage-all that is agreed upon should be detailed down in the file. The counsellor should moderate the discussions, if the pregnant woman has come with a partner or a caretaker; both of them should be involved in the discussions even if the care taker is not pregnant-if there is a caretaker present then this should be recorded and state the relationship between them.

Tick the areas that were discussed, mark with a cross what you did not discuss with her, note down important decisions that you have agreed upon with the participant-you will use this as a reference point in subsequent meetings and discussions

Ensure that the discussion does not exceed 30 minutes unless there is expressed interest from the participant to continue. And this expression should be noted down in the file.

For subsequent visits indicate appointment dates and actual revisit dates

Later on follow-up for delivery and record where she has delivered from

Assess for the different practices outlined annex 6 will be used to assess the following outcomes

Place of delivery, Cutting of the cord, care for the cord, initiation of breast feeding, provision of pre-lacteal feeds, in case of illness how it was recognised, what action was taken, how soon was the care seeking from onset of disease or when the decision was made that the child was unwell, what facility did she take the child, outcome, at the periphery of assessment the researcher will want to know whether the child is still alive just at one month.

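### The four-visit outcome depends partly on gestation at entry, which purposive allocation does not balance and which section 4.4.10 adjusts for only if it passes a significance screen

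*Protocol*

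**What the plan says.** **Entry.** Section 4.4.6 makes eligible "All pregnant women found to be up to 28 weeks of pregnancy in Masindi and Kiryandongo districts registered for ANC" at the 16 centres, with gestation taken from the last menstrual period and checked by fundal height. The enrolment procedure in Annex 15 (i) adds the condition "First visit of the current pregnancy", so enrolment is visit one and three more are needed.

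**Outcome.** Section 4.4.7 lists "Completion of the four recommended ANC visits" as an outcome, and sections 4.4.1 and 4.4.6 call it primary. The count is the same whatever the gestation at entry. Timely return is a separate primary outcome, defined as "return within seven days of the scheduled appointment date".

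**Schedule.** Annex 15 (i) says "For subsequent visits indicate appointment dates and actual revisit dates". No interval between appointments and no visit schedule by gestation is given.

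**Allocation and analysis.** Section 4.4.9 assigns eight centres to each arm purposively, at opposite extremes of the districts, to limit contamination. Section 4.4.10 runs chi-square tests and then puts only the variables that were significant at that stage into a logistic model. It ends by comparing the primary outcomes between arms, without saying which covariates that comparison carries. Gestation at entry is not named.

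**The concern.** Time left in pregnancy limits how many further visits a woman can make. If she enters near the cap and keeps each appointment, she may still deliver before the fourth and be recorded as not completing.

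Two consequences follow. Women in this position add non-completers to both arms, which dilutes any effect on attendance. More seriously, if women at one arm's centres tend to register later, completion will be lower there even when behaviour is identical. Randomisation of many centres would tend to balance entry gestation; purposive placement of eight against eight does not. A known, recorded determinant of a primary outcome then has no guaranteed place in its arm comparison.

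**Working it through.** **Plan's own figure.** The sample size rests on institutional delivery: 2.5 × (1.96 + 0.84)² × [0.235 × 0.765 + 0.335 × 0.665] / (0.335 − 0.235)² = 2.5 × 7.84 × 0.40255 / 0.01 = 789, matching the stated 788. (This uses the difference of the two rates in the denominator; the printed plus sign gives 24.) Then 789 × 1.10 = 868. The four-visit outcome plays no part in it.

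**Reachability.** With entry at week *g* and interval *i*, visit four falls at *g* + 3*i*. For entry at 28 weeks:

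- 3-week interval: week 37
- 4-week interval: week 40
- 5-week interval: week 43
- 6-week interval: week 46

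If she uses the full seven-day allowance each time and is rebooked from the actual visit, the four-week case moves to 28 + 3 × 5 = week 43. She would then be timely at every return she made and could still miss the fourth. The latest entry giving visit four by week 40, with appointments kept on the day, is week 31, 28, 25 or 22 for intervals of 3, 4, 5 or 6 weeks.

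**Share affected (assumptions, not document figures).** Gestation at birth is normal, mean 39.3 weeks, SD 1.9. Entry is split 17:45 between first and second trimester; the 17 is the national figure in section 1.4 and the 45 the local one in section 4.4.6. As a check, section 1.4 alone ("only 17% make the first visit in the first trimester; 34% of them initiate it late in the third trimester") leaves 49% for the second trimester, so 49/66 = 74% of women first seen before the third trimester; 45/62 is 73%. Within the second trimester, entry is either flat or rises towards the cap. Share unable to complete four visits with perfect attendance (flat to late-skewed entry):

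| Interval | Cap at 28.0 weeks | Cap at 28+6 |
|---|---|---|
| 3 weeks | 0.5–1.0% | 1.3–2.4% |
| 4 weeks | 5.6–10.2% | 8.6–15.4% |
| 5 weeks | 18–30% | 21–35% |
| 6 weeks | 32–49% | 35–52% |

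At four weeks this is about 49–89 of 868 per arm with the strict cap, or 75–134 counting to 28+6.

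**Bias from unequal entry.** Suppose each return has a 75% chance in both arms, so 0.75³ = 0.42 of women with enough time complete four visits. Move one arm's entry distribution two weeks earlier. The spurious difference in completion is:

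| Interval | Cap 28.0, flat to late-skewed | Cap 28+6, flat to late-skewed |
|---|---|---|
| 4 weeks | 1.8–3.2 points | 2.4–4.3 points |
| 5 weeks | 3.7–5.9 points | 3.7–5.6 points |
| 6 weeks | 4.1–5.0 points | 3.8–4.5 points |

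For example, at four weeks with a 28.0 cap and late-skewed entry, 0.42 × (1 − 0.102) gives 37.9%, against 41.1% in the earlier arm. At three-week intervals the difference cannot exceed 0.42 × 2.4% = 1.0 point.

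**The case against.** **The cap is deliberate.** Section 4.4.6 concedes that earlier attendance leaves more time and ties 28 weeks to the roughly 45% of local women who first attend in the second trimester. Section 5.1 lists the gestation restriction as a limitation. This stands as a reason for the cap. However, the reason concerns when women attend and the limitation concerns women left out; neither deals with how the outcome behaves among those admitted near the cap.

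**The outcome is reachable.** At four-week intervals or shorter, with birth at 40 weeks, a 28-week entrant can complete four visits. A reader might infer that the cap makes the outcome impossible for late entrants; the documents do not show that. Nor does section 2.3, which speaks of women "rarely completing the predetermined four visits for the entire gestation period", lay down a schedule spread across pregnancy. It gives a total.

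**Punctuality is measured separately.** True: completing four visits is a different outcome and the service indicator the trial wants to move. That explains why it is kept, but does not remove its dependence on entry gestation.

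**The screen would usually catch it.** If gestation drives completion strongly, with 1,736 women it would normally be significant and enter the model. This is largely right, and it limits the severity. Covariate lists are also commonly left to an analysis plan. But section 4.4.10 does fix a selection rule, and under it a confounder's place depends on a p-value.

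**Conclusion.** The point holds in a limited form. Completion of four visits depends partly on gestation at entry, entry gestation is not balanced by design, and the stated rule does not guarantee adjustment for it.

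The size is conditional. The share who could not complete ranges from about 1% to about half of entrants, depending on an interval the protocol does not give; 6–10% (strict cap) or 9–15% (to 28+6) is the four-week case. The 2–6 point bias needs a two-week difference between arms, which is hypothetical; nothing in the documents shows that one exists.

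A reader might go further and confine the main comparison to women entering by about 24 weeks. The documents do not support that. Under the four-week assumption, 60–72% of women entering after 24 weeks could still complete four visits, and the protocol chose to include them. Nor is the sample size affected, since it rests on institutional delivery.

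**What to change.** In section 4.4.10, state that for the completed-four-visits outcome the arm comparison includes gestation at first visit as a pre-specified covariate, whatever its bivariate significance. Fix its form in advance; the working suggests completion falls faster close to the cap, so a form that permits this is better than a single linear term.

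Keep all enrolled women in the main comparison. At most, add a sensitivity analysis in women whose entry gestation leaves time for four visits at the clinics' actual appointment interval, with the cut set on that baseline value before analysis.

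The cost is a sentence or two of text. Gestation must be established in both arms to apply the eligibility rule, and Annex 15 (i) already records it at first visit. Enrolment, the other outcomes and the sample size stay as they are. The covariate deals only with entry gestation and does not cure other imbalances that purposive allocation may bring.
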